### **8.3.1 Randomization procedure**

Sixty plain envelopes numbered from 1 to 60 for each site are provided by the Swedish Institute for Infectious Disease Control which is responsible for the vaccine/placebo product supply. They will be divided in 6 sets of 10 envelopes. Each set will contain 3 assignments to Group IA, 3 to Group IIA and 3 to Group IIIA and 1 to either of Group IB, IIB or IIIB. Group numbers refer to the immunization schedule. The study Pharmacist will take the prepared envelopes and put them in a box that is kept under lock. The pharmacist will randomize participants accepted into the study by selecting the next consecutive envelope containing the vaccine or placebo assignment in accordance with the generated randomization list. This will be documented in **CRF 8-I** pharmacy copy. The Pharmacist will then inform the Study Nurse/medical officer at the clinic of the randomization group of the volunteer (2x versus 5x i.d. DNA priming) on the **CRF 8-II** clinical copy, including the number of the envelope, but will not inform on whether this is vaccine or placebo. The Study Nurse will record the envelope number and the group assignment (2x versus 5x i.d. DNA priming) into a register book, the medical record file (source document), as well as the outer cover of the participant's file.

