## **6 METHODOLOGY**

### **6.1 Study design**

This is a randomized, controlled, double blinded study with regard to placebo/vaccine but not group.

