## 6.6 Randomization procedure

Block randomization in blocks of 10 with a ratio of 9 vaccine recipients to a single placebo will be used with equal distribution among the two sites.

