### **8.3.2 Blinding procedure**

The vaccines will be kept in the department of Microbiology/Immunology at MUHAS or at the study pharmacy at NIMR-MMRP under appropriate storage conditions according to manufacturer's specifications. The study pharmacist who has access to the code will draw the study vaccine and the placebo into syringes and label them with the study number, the site, randomization group of the volunteer (2x versus 5x) and participant code, date and time and hand them over to the study nurse for injection. Nurses administering the vaccines, all other site investigators and lab personnel as well as the participants themselves will be blinded to the type of vaccine that the participant will be receiving.

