### **20.1 Analysis**

All safety end-points will be graded by the Clinical Investigator and reviewed by the Trial Management Group. Any queries about grade and relationship to study product that cannot be resolved will be referred to the Trial Coordinating Committee for a final decision.

The primary safety end-points are: The safety of immunization with the seven DNA plasmids carrying HIV-1 genes as assessed by clinical signs, and standard clinical chemistry/hematological laboratory tests where any worsening of the severity grade will be considered for causality by the vaccine.

The alternative immunization applications (2x i.d. versus 5x i.d. with the Biojector device) will be evaluated for adverse events by assessing local (pain, cutaneous including indurations),

general (fever, chills, headache, nausea, arthralgia, malaise, myalgia) and other unsolicited adverse events within 7 days.

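### The fixed envelope sets in section 8.3.1, read against the 2x/5x record kept in the clinic, reveal 48 of 108 vaccinees and so partly break the vaccine/placebo blind for clinic staff

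*Protocol*

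**What the plan says.** Section 6.1 describes a "double blinded study with regard to placebo/vaccine but not group": the regimen may be seen, but vaccine versus placebo may not. Section 8.3.2 extends the mask to the nurses who inject and adds that "all other site investigators and lab personnel as well as the participants themselves will be blinded to the type of vaccine".

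The allocation is set out in sections 6.6 and 8.3.1:

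- Section 6.6: "Block randomization in blocks of 10 with a ratio of 9 vaccine recipients to a single placebo".
- Section 8.3.1: "Sixty plain envelopes numbered from 1 to 60 for each site are provided", and "They will be divided in 6 sets of 10 envelopes".
- Section 8.3.1: "Each set will contain 3 assignments to Group IA, 3 to Group IIA and 3 to Group IIIA and 1 to either of Group", where the single assignment goes to one of the three placebo groups (IB, IIB, IIIB). The pharmacist opens the envelopes in numerical order.
- Section 8.3.1: the clinical copy of the randomisation form gives the clinic the 2x/5x group and the envelope number. "The Study Nurse will record the envelope number and the group assignment (2x versus 5x i.d. DNA priming) into a register book", and also in the source file and on the front of the participant's folder.

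The table in section 6.5 gives IB and IIB placebo as two saline injections and IIIB placebo as five, so each placebo carries the same visible label as its vaccine group. On safety, section 20.1 says: "All safety end-points will be graded by the Clinical Investigator".

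**The concern.** The blind rests on the 2x/5x label saying nothing about vaccine or placebo. In this scheme it does say something. The vaccine content of a set is constant (six 2x, three 5x), so the only thing that can move the tally is the label of the single placebo. Anyone with the protocol and the clinic register can read off which label the placebo carries, and then knows that everyone in that set with the other label had vaccine. No code break is needed.

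What is at stake is judgement at the clinic. The clinical investigators grade events and assign relatedness, and relatedness enters the criteria for withdrawal from injections (section 16.1) and for pausing the study (section 16.2). A grader who knows that a participant had vaccine may grade or attribute differently, and that would colour any contrast with the 12 placebo recipients.

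The sponsor already guards against unblinding by inference. Sections 8.1.4 and 17.2 and Appendix 7 restrict HIV results to infected or not infected, so that a false positive does not give the allocation away. The envelope scheme leaves a comparable route open.

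**Working it through.** **Inputs**

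- Envelopes: 60 per site, two sites, sets of ten (section 8.3.1), so 120/10 = 12 sets.
- Each set: 3 IA + 3 IIA + 3 IIIA + 1 placebo (section 8.3.1).
- Placebos: 4 IB, 4 IIB, 4 IIIB (section 6.5), so 8 carry the 2x label and 4 the 5x label.

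**Reproducing the plan's group sizes**

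12 × 3 = 36 in each of IA, IIA and IIIA, which is 108 vaccinees. 12 × 1 = 12 placebos = 4 + 4 + 4. The total is 120, as in section 6.5.

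**Tally by type of set**

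| Placebo in set | Sets | 2x : 5x | Certain vaccinees per set | Chance of placebo for the rest |
|---|---|---|---|---|
| IB or IIB (2x) | 8 | 7 : 3 | 3 (all the 5x) | 1/7 = 14.3% |
| IIIB (5x) | 4 | 6 : 4 | 6 (all the 2x) | 1/4 = 25% |

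**Number identified**

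8 × 3 + 4 × 6 = 24 + 24 = 48; 48/108 = 44.4%.

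Check on the remainder: 8 × 7 + 4 × 4 = 56 + 16 = 72 participants, who hold 56/7 + 16/4 = 8 + 4 = 12 placebos. All the placebos are accounted for, and 72 − 12 = 60 vaccinees are not identified.

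The 48 does not depend on how placebo types are divided between sites. With s sets holding a 5x placebo the count is 3(12 − s) + 6s = 36 + 3s, and section 6.5 fixes s = 4.

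**When it becomes known**

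The type of a set is settled when the seventh 2x or the fourth 5x envelope appears. In random order the expected position of the last of k items among ten is 11k/(k + 1).

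- 7:3 sets: 11 × 7/8 = 9.625.
- 6:4 sets: 11 × 4/5 = 8.8.
- Over all sets: (8 × 9.625 + 4 × 8.8)/12 = 9.35.
- Settled before the tenth envelope: probability 3/10 in 7:3 sets and 6/10 in 6:4 sets; (8 × 0.3 + 4 × 0.6)/12 = 40%.
- Vaccinees known before their own first dose: 3/8 per 7:3 set and 6/5 per 6:4 set; 8 × 0.375 + 4 × 1.2 = 7.8, about 8 of the 48. A simulation gave the same figures.

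With 60 participants per site enrolled evenly over 12 months (sections 6.3 and 6.4), a set fills in about 12/6 = 2 months. On that assumption the set is settled before both MVA injections, at weeks 30 and 46.

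**The case against.** A reader might infer that the scheme defeats the double blind altogether, and with it the primary results. The documents do not support that, for these reasons:

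- **No placebo recipient is identified.** All 12 stay hidden among 72 participants. The 9:1 ratio is printed, so staff already know that any participant has a 90% chance of vaccine. Counting takes 48 people from 90% to 100%; it does not take anyone from ignorance to knowledge. This stands and limits the harm.
- **The laboratory and the cardiologists are not shown to see the tally.** Sample labels (section 8.1.6) carry neither envelope number nor group, and nothing in sections 8.12 or 12.1.4 gives envelope numbers to the ECG panel. This stands: exposure of the ELISPOT endpoint or of the panel's readings is not demonstrated.
- **The powered comparison is between vaccine groups.** Section 20 sizes IA and IIA against IIIA, and section 6.1 leaves the group unmasked. This stands: that comparison does not rest on the vaccine/placebo mask.
- **There is independent review.** Section 17 assigns a medical monitor to each site, and section 19.2.1 gives the coordinating committee, and possibly an independent end-point committee, a say in grade and relatedness. This stands in part: they act on events that clinic staff have already described and graded.
- **Someone has to count, and in about 60% of sets nothing is settled until the tenth envelope.** True, but all the material needed is in the protocol and in a register that the protocol requires. Follow-up runs well beyond the first dose.

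**Conclusion.** The scheme partly breaks the vaccine/placebo blind for clinic staff, contrary to sections 6.1 and 8.3.2. Once their sets fill, 48 of 108 vaccinees (44%) are known with certainty. For the other 72 participants the chance of placebo moves from 1/10 to 1/7 or 1/4. If a placebo recipient is recognised by some other route, the nine others in that set are known at once.

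The consequence is confined to adverse-event grading and relatedness judgements by nurses and clinical investigators, and to the withdrawal and pause criteria that use them. The documents give no basis for putting a figure on the resulting bias.

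The count assumes that a set is ten consecutive envelope numbers, which the blocks of ten and the numerical order of use support, and that all sets are filled. Uneven recruitment between sites (section 6.4) or replacement of withdrawals (section 8.22) could change it by a few. The timing also assumes even accrual. Allocation and what the clinic is shown are fixed in the protocol, so no later analysis can restore the mask at the moment of grading.

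**What to change.** Regenerate the list so that the visible label carries no information about vaccine or placebo. At each site, randomise participants to I, II or III in blocks. Separately, within each group, allocate vaccine to placebo 18:2, as two blocks of ten at 9:1.

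Each site then has 20 per group. Its 5x label covers 20 participants with 2 placebos, and its 2x label covers 40 with 4. Both are 1/10, whatever the tally of any run of envelopes, so counting identifies nobody. Over two sites the totals remain 36:4 per group and 9:1 overall, with the sites equal. Rewrite the set description in section 8.3.1 to match.

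Keeping the envelope number on the pharmacy copy only is an optional extra. Alone it would do little, because envelopes are used in order and a clinic can count its own enrolments. It would also remove a cross-check between clinic and pharmacy.

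The cost is a new list and one edited paragraph, with no added participants or staff. The downside is slightly looser vaccine-to-placebo balance within each run of ten enrolments. If some envelopes have already been opened, only the unopened ones can be replaced, with the remaining numbers chosen to reach 36:4 in each group.

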### **8.3.2 Blinding procedure**

The vaccines will be kept in the department of Microbiology/Immunology at MUHAS or at the study pharmacy at NIMR-MMRP under appropriate storage conditions according to manufacturer's specifications. The study pharmacist who has access to the code will draw the study vaccine and the placebo into syringes and label them with the study number, the site, randomization group of the volunteer (2x versus 5x) and participant code, date and time and hand them over to the study nurse for injection. Nurses administering the vaccines, all other site investigators and lab personnel as well as the participants themselves will be blinded to the type of vaccine that the participant will be receiving.

### **8.3.3 Vaccination**

Prior to the first vaccination the enrolled study participant will receive an abbreviated risk assessment and risk behavior counseling as well as pre HIV test counseling prior to HIV testing. Vital signs will be recorded and blood will be donated according to the visit schedule (safety laboratory tests, urine dip stick, HIV test, CD4 count and baseline immunogenicity tests) including pre vaccination pregnancy test from urine for female participants. The participants will then attend the medical officer who will evaluate the pre vaccination medical status (**CRF 3-II**).

A pregnancy test for female participants before each vaccination will have to show negative results *before* vaccination.

After confirming the medical eligibility for vaccine administration including a negative pregnancy test for female participants the vaccine request form (**CRF 10-II**) will be filled by the medical officer, transferred to the pharmacist who will then deliver to the nurse the appropriate vaccine/placebo that corresponds to the assigned group. The participant will then receive the first injection. After vaccination the participants will be observed for 30 minutes at the clinic for potential early adverse reactions (anaphylactic reactions). Follow-up and safety procedures as well as distribution and handling of diary cards will be performed. A detailed description of the post vaccination procedures is provided in the protocol section **Immunization** further below.

The participant will then be compensated and assigned to his next scheduled visit.

#### **8.4 Study visit 4 – Follow up**

##### **(Study week 2; 14 days after V3 +/- 3 days)**

This is the follow up visit two weeks post 1st DNA/Placebo vaccination. It is essentially a safety assessment visit conducted by both study nurse(s) and study doctor(s) (**CRF 2-III**). At this visit diary cards will be collected by study nurses and discussed with the participants addressing also problems and deficiencies arrived within in recording process. Assistance and explanation will be again provided and sufficient time given for questions and answers. HIV posttest counseling and risk behavior counseling will be performed as well as recording of vital signs. Blood will be donated according to the flow chart. The participant will then attend the medical officer who will revise the diary card and discuss potential adverse reactions documented. Diary entries will be transcribed into the vaccine reaction form (**CRF 10-1**). The medical status will be evaluate and documented (**CRF 3-II**), new or changed medication (**CRF 4-I**) as well as medical events (**CRF 6-I**) since the last visit will be recorded. All medical conditions (symptoms and/or diagnosis) that are not defined and indicated in the vaccine reaction form (**CRF 10-1**) will be recorded in the adverse events form (**CRF 6-I**) including the severity grade and the relationship to the study agent. The participant will then be compensated and assigned to his next scheduled visit.

#### **8.5 Study visit 5 – Vaccination II (2nd DNA/Placebo)**

##### **(Study week 4; 28 days after V3 +/- 3 days)**

The visit is for the second DNA/Placebo injection of the study vaccine and is conducted by both the study nurse and the study doctor (**CRF 2-III**). An abbreviated risk assessment and risk behavior counseling as well as pre HIV test counseling will be performed, vital signs will be recorded and blood will be donated according to the visits schedule including pre vaccination pregnancy test for female participants. The vaccination procedures including pre- and post vaccination assessments will be conducted as described above.

#### **8.6 Study visit 6 – Follow up**

##### **(Study week 6; 14 days after V5 +/- 3 days)**

This is the first follow up visit two weeks post 2nd DNA/Placebo vaccination. It is essentially a safety assessment visit and will be conducted as described for study visit 4. Post HIV test counseling will be performed, diary cards discussed, blood drawn according to the flow chart and participants will be seen by the medical officer for medical status recording and diary transcription. The forms will be filled according to the visit schedule checklist. The participant will then be compensated and assigned to his next scheduled visit.

#### **8.7 Study visit 7 – Follow up**

##### **(Study week 8; 28 days after V5 +/- 5 days)**

This is the second follow up visit post 2nd DNA/Placebo vaccination. It is essentially a safety assessment visit and will be conducted by the study nurse(s) and the study doctor. Abbreviated risk assessment and risk behavior counseling will be done, vital signs performed, blood drawn according to the flow chart and participants will be seen by the medical officer for medical status recording. CRF's are filled according to flow chart. The participant will then be compensated and assigned to his next scheduled visit.

#### **8.8 Study visit 8 – Vaccination III (3rd DNA/Placebo)**

##### **(Study week 12, 84 days post V3 +/- 7days)**

This visit is for the 3rd DNA/Placebo vaccination and is conducted by both the study nurse and the study doctor and will be conducted as described above.

#### **8.9 Study visit 9 – Follow up**

##### **(Study week 14; 14 days after V8 +/- 3 days)**

This is the first follow up visit two weeks post 3rd DNA/Placebo vaccination. It is essentially a safety assessment visit and will be conducted as described for study visit 4. Blood draw and

filling of forms will be done according to the visit schedule. The participant will then be compensated and assigned to his next scheduled visit.

**8.10 Study visit 10 – Follow up**  
**(Study week 16; 28 days after V8 +/- 5 days)**

This is the second follow up visit post 3rd DNA/Placebo vaccination. It is essentially a safety assessment visit and will be conducted as described for study visit 7. Blood draw and filling of forms will be done according to the visit schedule. The participant will then be compensated and assigned to his next scheduled visit.

**8.11 Study visit 11 – Vaccination IV (1st MVA/Placebo)**  
**(Study week 30; 126 days post V8 +14/-28 days)**

The visit is for the first MVA/Placebo injection of the study vaccine conducted by both the study nurse and the study doctor and will be conducted as described above. The participant will then be compensated and assigned to his next scheduled visit.

**8.12 Study visit 12 – Follow up**  
**(Study week 32; 14 days after V11 +/- 3 days)**

This is the first follow up visit two weeks post 1st MVA/Placebo vaccination. It is essentially a safety assessment visit and will be conducted as described for study visit 4. Blood draw and filling of forms will be done according to the visit schedule. In addition a post vaccination ECG will be performed and results will be interpreted and compared to baseline ECG results by competent study physicians and send to the cardiologist panel for review and approval. Post vaccination ECG will be graded as *normal*, *abnormal/clinically insignificant* and *abnormal/clinically significant*. Post vaccination ECG findings will be graded as *no changes*, *changes/not significant* and *changes/significant* as compared to baseline results. Clinical chemistry analysis will include a Troponin I test. The participant will then be compensated and assigned to his next scheduled visit.

**8.13 Study visit 13 – Follow up**  
**(Study week 34; 28 days after V11 +/- 5 days)**

This is the second follow up visit post 1st MVA/Placebo vaccination. It is essentially a safety assessment visit and will be conducted as described for study visit 7. Blood draw and filling of forms will be done according to the visit schedule. The participant will then be compensated and assigned to his next scheduled visit.

**8.14 Study visit 14 – Vaccination V (2nd MVA/Placebo)**  
**(Study week 46; 168 days post V11 +14/-28 days)**

The visit is for the second MVA/Placebo injection of the study vaccine conducted by both the study nurse and the study doctor and will be conducted as described for Visit 11. The participant will then be compensated and assigned to his next scheduled visit.

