### The vaccine (immunogens)

Priming with a plasmid having HIV-1 DNA encoding the following genes:

1. Pool 1
  - a. env, from HIV-1 subtypes A, B, C
  - b. rev, from HIV-1 subtype B
2. Pool 2
  - a. gag, from HIV-1 subtypes A, B
  - b. RTmut (enzymatically inactive mutated reverse transcriptase), from HIV-1 subtype B

Boosting will be effected by a Modified Vaccinia Ankara vaccine (MVA-CMDR). It is a attenuated recombinant poxvirus vector that has been genetically engineered to express the following HIV-1 genes:

1. gp150 (Subtype E, CM235), and
2. gag and pol (integrase-deleted and reverse transcriptase nonfunctional, Subtype A, CM240).

HIV-DNA/placebo will be given at weeks 0, 4 and 12 as intradermal injections. Two HIV-MVA/placebo boost injections will be given intramuscularly at 18 and 34 weeks after the last (third) DNA/placebo priming injection, ie at week 30 and 46 respectively.

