### Duration of study

The enrolment period is planned to be 12 months.

The volunteers will be monitored through week 24 after the last injection ie a total of 70 weeks.

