#### **8.18 Study visit 18 – Final study visit (Study week 70; 168 days post V14 +/- 14 days)**

This is the second long time follow up visit after the completed vaccination schedule and the final study visit. It is essentially a safety and immunogenicity assessment visit. The study nurse(s) and the study doctor will conduct it. Pre HIV test counseling and extended risk assessment and risk behavior counseling is performed. Vital signs will be recorded and blood will be drawn according to the flow chart. The medical officer will conduct a medical status examination and forms will be filled according to the visit schedule including the disclosure of the Patients Status Form (**CRF 7-I**), the Concomitant Medication Form (**CRF 4-I**) and the Adverse Events Form (**CRF 6-I**). Ongoing or new medical events if not related to the study agents will be reported and might be followed up in 1 or 2 additional unscheduled visits but should preferentially be referred to the appropriate health facilities for further management. In the case of ongoing pregnancies study visits will proceed as unscheduled visits until pregnancy and infant outcome can be recorded. Volunteers may be asked to participate in long-term follow-up studies. All study volunteers will be issued a card signed by the principal investigators (full names, tel. numbers and addresses) stating that the holder has participated as a volunteer in a HIV-1 immunization study and that the outcome of standard HIV diagnostic tests do not signify HIV-1 infection. Study participants will be invited to perform HIV testing if wished by the study site also after the completion of the study.

Post HIV test counseling will be performed 2-3 weeks after this visit only by the nursing/counseling staff in the case of negative test results. This post HIV test contact will be recorded as an additional study visit (Visit 18J) and compensated as indicated for unscheduled visits.

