## 9 IMMUNIZATION

### 9.1 Immunization schedule

While DNA/Placebo immunizations will be performed at weeks 0, 4 and 12, MVA/Placebo will be given at weeks 30 and 46. The immunization schedule is summarized below:

| Study week                                              |    | 0                                                                                                             | 4                                                                                                                 | 12                                                                                                                 | 30                                                              | 46                                                               |
|---------------------------------------------------------|----|---------------------------------------------------------------------------------------------------------------|-------------------------------------------------------------------------------------------------------------------|--------------------------------------------------------------------------------------------------------------------|-----------------------------------------------------------------|------------------------------------------------------------------|
| Injection schedule in days
+/- acceptable time frame |    | 0                                                                                                             | 28 days (+/-3)
post DNA I                                                                                      | 84 days (+/- 7)
post DNA I                                                                                      | 126 days post V8 +14 /-28
days                               | 112 days post V11
+14 /-28 days                               |
| Study Group                                             | N  | 1 st vaccination                                                                                   | 2 nd vaccination                                                                                       | 3 rd vaccination                                                                                        | 4 th vaccination                                     | 5 th vaccination                                      |

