## **15            PROTOCOL DEVIATION**

Any deviation of the study schedule or study protocol will have to be recorded in the appropriate case report form (**CRF 7-II**) including the date, a description, the category and the reason of the deviation. Also a description of potential steps taken to resolve deviation or how to avoid recurrence should be attempted. These deviation should be reported to the study monitor, sponsor, TCC, WRAIR and DSMB within 2 working days. The TCC, WRAIR and DSMB will review and make the appropriate recommendations to the monitor, who will transmit these to the sponsor. Records of these reports will be submitted to the, Steering committee, TCC, the local IRB, NIMR and TFDA at regular intervals.

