| 213        |      | V11E  | Day 3 post vaccination                         |                                |
| 214        |      | V11F  | Day 4 post vaccination                         |                                |

|     |    |      |                                   |                                 |
|-----|----|------|-----------------------------------|---------------------------------|
| 215 |    | V11G | Day 5 post vaccination            |                                 |
| 216 |    | V11H | Day 6 post vaccination            |                                 |
| 217 |    | V11I | Day 7 post vaccination            |                                 |
| 224 | 32 | V12  | Follow-up safety + immunogenicity | 14 days post V11 +/- 3 days     |
| 238 | 34 | V13  | Follow-up safety                  | 28 days post V11 +/- 5 days     |
| 322 | 46 | V14  | MVA II + immunogenicity           | 112 days post V11 +14 /-28 days |
| 322 |    | V14A | 30 min post vaccination           |                                 |
| 322 |    | V14B | Evening of vaccination day        |                                 |
| 323 |    | V14C | Day 1 post vaccination            |                                 |
| 324 |    | V14D | Day 2 post vaccination            |                                 |
| 325 |    | V14E | Day 3 post vaccination            |                                 |
| 326 |    | V14F | Day 4 post vaccination            |                                 |
| 327 |    | V14G | Day 5 post vaccination            |                                 |
| 328 |    | V14H | Day 6 post vaccination            |                                 |
| 329 |    | V14I | Day 7 post vaccination            |                                 |
| 336 | 48 | V15  | Follow-up safety + immunogenicity | 14 days post V14 +/- 3 days     |
| 350 | 50 | V16  | Follow-up safety + immunogenicity | 28 days post V14 +/- 5 days     |
| 406 | 58 | V17  | Follow-up immunogenicity          | 84 days post V14 +/- 14 days    |
| 490 | 70 | V18  | Follow-up immunogenicity          | 168 days post V14 +/- 14 days   |

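### Section 8.14 puts the second MVA boost 168 days after Visit 11, but its own week-46 label and every other schedule statement give 112 days, and the two windows do not overlap

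*Protocol*

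**What the plan says.** Section 8.14 of the Protocol gives the timing of Visit 14, the second MVA/placebo injection, as "Study week 46; 168 days post V11 +14/-28 days".

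The other statements of the same interval are:

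- Section 9.1, the immunization schedule, puts the MVA injections at weeks 30 and 46 and times the second at "112 days post V11", with the same +14/-28 tolerance.
- Appendix 1 lists Visit 14 at target day 322, week 46, "112 days post V11 +14 /-28 days".
- Appendices 2 and 3 give target day 210 for Visit 11 and day 322 for Visit 14.
- The synopsis places the two boosts "at 18 and 34 weeks after the last (third) DNA/placebo priming injection, ie at week 30 and 46 respectively". Section 6.5 gives the same 18 and 34 weeks.
- On duration, the synopsis says: "The volunteers will be monitored through week 24 after the last injection ie a total of 70 weeks".
- Section 8.18 times the final visit at "Study week 70; 168 days post V14 +/- 14 days".

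Section 15 says what follows from missing a window: "Any deviation of the study schedule or study protocol will have to be recorded in the appropriate case report form". Such deviations go to the monitor, the sponsor, the coordinating committee, the MVA supplier and the DSMB within 2 working days.

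**The concern.** Section 8.14 is the procedural instruction for a vaccination visit, and its visit window is expressed in days from the previous dose. If that day count is wrong, the Protocol contains two rules for one injection. A boost that is on time under one section is a deviation under the other, and section 15 makes each deviation reportable.

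Staff who apply the 168 would also give the boost about 8 weeks late. The primary ELISPOT is read 2 weeks after the second MVA (section 20), so it would move with the boost, and follow-up would run past the stated 70 weeks. With two sites dosing under the same text, the interval between the MVA injections could differ from one participant or site to another.

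**Working it through.** This is calendar arithmetic.

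**Inputs.** Visit 8 is day 84, week 12 (section 8.8). Visit 11 is 126 days after Visit 8 (section 8.11). Visit 15 is 14 days after Visit 14 (section 8.15). Visit 18 is 168 days after Visit 14 (section 8.18). The tolerance for Visit 14 is +14/-28 days in all three places that state one.

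**Visit 11.** 84 + 126 = day 210, and 210 / 7 = week 30, which agrees with section 8.11.

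**Interval implied by the other statements.**

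- Week labels: (46 - 30) × 7 = 112 days.
- Weeks after the third DNA dose: (34 - 18) × 7 = 112 days.
- Target days in the appendices: 322 - 210 = 112 days.
- Study duration: 70 weeks is day 490. Subtracting the 168 days from Visit 14 to Visit 18 gives day 322, and 322 - 210 = 112 days.

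**Both intervals carried through the schedule, with Visit 11 on day 210.**

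| | 168 days (8.14) | 112 days (9.1, Appendix 1) | Week stated in section 8 |
|---|---|---|---|
| Visit 14 | 210 + 168 = day 378, week 54 | 210 + 112 = day 322, week 46 | 46 |
| Visit 15 (primary ELISPOT) | 378 + 14 = day 392, week 56 | 322 + 14 = day 336, week 48 | 48 |
| Visit 18 | 378 + 168 = day 546, week 78 | 322 + 168 = day 490, week 70 | 70 |

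The 168 does not reproduce the week printed beside it. The 112 reproduces all three stated weeks.

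**Windows, in days after the participant's own Visit 11.**

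- Section 8.14: 168 - 28 = 140 to 168 + 14 = 182.
- Section 9.1 and Appendix 1: 112 - 28 = 84 to 112 + 14 = 126.
- Gap: 140 - 126 = 14 days.

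Both windows start from the same Visit 11 date, so an early or late Visit 11 shifts them together and cannot create an overlap.

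**Spread of the interval if both rules were in use.** The intended window permits 126 - 84 = 42 days between the earliest and latest boost. With some participants dosed under each rule, the possible range becomes 182 - 84 = 98 days.

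**The case against.** The strongest reply is that the intended value is not in doubt. The 168 stands alone against the week number in the same heading, the section devoted to the immunization schedule, three appendices and the synopsis. Section 8 itself sends readers to Appendices 1 to 3 for an overview. To dose late, staff would have to use the day count and disregard all of these, and nothing in the Protocol shows that either site would. This stands: late dosing and spurious deviations are possible consequences, not demonstrated ones. It does not remove the error, because the wrong figure is the one that defines the window in the visit's own instruction.

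A second reply is that the statistical effect is close to nil. Visit 15 stays 14 days after the actual Visit 14, so the time from boost to ELISPOT is unchanged. On allocation, section 8.3.1 says of the envelopes: "Each set will contain 3 assignments to Group IA, 3 to Group IIA and 3 to Group IIIA". These sets are made up separately for each site, so the arms stay balanced even if the sites used different intervals. The intended window also already accepts a 42-day spread. All of this stands and limits the weight of the point.

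A third reply concerns study weeks. With Visit 11 on day 210, the earliest boost under section 8.14 is 210 + 140 = day 350, week 50. If Visit 11 fell 28 days early, on day 182, the earliest date would be 182 + 140 = day 322, which is week 46. So section 8.14 does not exclude week 46 for every participant. That is correct, but compliance is judged in days from Visit 11, and on that scale the windows never meet.

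**Conclusion.** The concern holds. The 168 days in section 8.14 is wrong as written, and the correct figure is 112. The targets differ by 168 - 112 = 56 days, and the two windows are separated by 14 days, so no Visit 14 date complies with both. The week numbers quoted for the consequences assume Visit 11 on its target day; the conflict between windows needs no such assumption.

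It should be fixed because it sets a dosing window and triggers reportable deviations. It does not threaten the validity of the randomised comparisons, and nothing in it changes the endpoint definition or the sample size.

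The figure may be left over from a longer schedule. Section 8.1.1 refers to a changed visit schedule, and sections 17.2 and 20.2 still cite weeks 84 and 108. That is an inference, and the conclusion does not depend on it.

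**What to change.** In the heading of section 8.14, replace 168 with 112 days after Visit 11 and keep the +14/-28 tolerance. Visits 14, 15 and 18 then fall on weeks 46, 48 and 70, as stated elsewhere.

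Notify both sites, before the first Visit 14 if that is still possible. The Protocol does not show how far the trial had progressed at this version. If any second boosts have already been given, check which interval was applied and classify deviations against the 84-to-126-day window.

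The cost is one number in one heading, by amendment or clarification letter.
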